## Abstract

**Background:**

Youth social anxiety is rising; however, evidence for therapist-guided virtual reality (VR) exposure remains sparse.

**Objective:**

This randomized controlled trial will test whether such a VR program is associated with reductions in social-anxiety symptoms in youth aged 15 to 25 years.

**Methods:**

Participants will be recruited from schools, tertiary institutions, and community centers in Hong Kong and screened for eligibility. Youth aged 15 to 25 years who score 25 or higher on the Social Phobia Inventory (SPIN) will be randomly allocated to either the VR intervention group or the waitlist control group in a 1:1 ratio. The VR group will receive a 6-session therapist-facilitated VR intervention, focusing on exposure to realistic social scenarios, real-time physiological monitoring, and AI-driven adaptive support. The control group will not receive the VR intervention during the primary assessment period but will be offered access after the 3-month follow-up assessment. Both groups will be assessed at baseline, 1 month (postintervention), and 3 months for the primary outcome of social anxiety (SPIN) and the secondary outcome of depression (Patient Health Questionnaire-9). An exploratory cost analysis will estimate the cost per unit reduction in SPIN scores.

**Results:**

A total of 90 participants (45 in each group) will be recruited. Participant enrollment began in March 2026, and data collection will continue until the required sample size is reached. The primary findings are expected to be published in late 2027. Outcome analyses will use a linear mixed effects model under the intention-to-treat principle, with missing data accounted for under the assumption of missing-at-random.

**Conclusions:**

This trial will provide preliminary evidence on the efficacy, feasibility, and acceptability of a therapist-facilitated VR intervention for youth social anxiety in Hong Kong. Given the waitlist comparator and 3-month follow-up period, findings will not establish VR-specific effects, long-term effectiveness, or implementation-level cost-effectiveness.

## Introduction

### Social Anxiety Among Youth

Social anxiety, also known as social phobia, is characterized by a marked fear of social situations where individuals may be scrutinized by others, often leading to avoidance behaviors and distress [1,2]. It, often arising in adolescence, is among the most common anxiety disorders affecting youth and can substantially disrupt academic performance, peer relationships, and emotional well-being [3,4]. A central feature of social anxiety is extreme sensitivity to negative evaluation, perpetuating cycles of self-doubt and anticipatory anxiety [4]. Among young people, persistent concerns over potential judgment can lead to social withdrawal and diminished social support, thereby exacerbating loneliness and isolation [5]. Indeed, in an investigation involving adolescents and young adults, researchers found that social anxiety often manifests before major depression, underscoring the urgent need for early screening and targeted interventions in this population [6].

### Therapist-Facilitated Virtual Reality Interventions

Virtual reality (VR)–based interventions provide immersive and controllable environments in which anxiety-provoking social or performance situations can be simulated [7,8]. For youth with social anxiety, VR may be particularly useful because feared situations can be presented gradually, repeated safely, and adjusted according to the participant’s level of difficulty; however, youth-specific evidence remains limited and requires further controlled evaluation [9]. Compared with in vivo exposure alone, VR may reduce some practical barriers by allowing exposure tasks to be delivered in a private and standardized setting, although transfer to real-world functioning should be examined empirically rather than assumed [7,8,10]. Therapist facilitation may further strengthen VR-based interventions. A trained therapist can help participants identify feared predictions and safety behaviors, prepare for exposure tasks, monitor distress, and consolidate learning through debriefing and homework planning [11,12]. However, evidence on therapist-facilitated VR interventions for youth social anxiety remains limited, and the extent to which symptom improvement transfers to daily functioning requires further empirical investigation [9,10].

### Research Gaps

Robust evidence on VR treatment for adolescent social anxiety is still sparse, particularly from randomized controlled trials (RCTs). This gap is noteworthy because adolescents, often described as “digital natives,” are generally receptive to technology-mediated care—a factor that can boost both engagement and adherence [9]. Although a small body of research indicates that self-guided VR programs can reduce anxiety by providing convenient, on-demand, and relatively low-cost exposure practice [7,8], the added value of therapist-facilitated VR remains largely untested. In a guided format, clinicians can give real-time feedback, fine-tune exposure tasks, and address comorbid issues such as cognitive distortions or emotional dysregulation as they emerge [13]. This active professional involvement is likely to improve treatment adherence, deepen therapeutic engagement, and optimize clinical outcomes by keeping the exposure simultaneously challenging and safely supported [13].

Additionally, the lack of economic evaluations for VR-based psychological interventions is a critical issue, particularly during times of global economic downturns, when funding for mental health support and research often declines [14]. Without rigorous cost-effectiveness analyses, policymakers may face challenges in allocating resources efficiently, potentially limiting access to innovative digital interventions that could provide scalable, engaging, and sustainable mental health support for young individuals. Addressing these gaps is important for understanding whether VR interventions can be both potentially useful and feasible for broader use in youth mental health care [15].

### Research Objectives and Hypotheses

Our aim is to test the preliminary efficacy of a therapist-facilitated VR intervention for reducing social anxiety symptoms among young individuals, compared with a waitlist control condition. The primary research question is: “Does the therapist-facilitated VR intervention, when compared to waitlist group, result in a reduction of social anxiety symptoms among youths at 1-month (post-treatment) and 3-month follow-up?” Additionally, the study aims to investigate the cost-effectiveness of this intervention by determining “What is the cost per unit reduction in the SPIN score (if applicable)?” The study does not aim to establish implementation effectiveness in routine service settings or definitive generalization to real-world behavior. Our hypotheses are as follows:

H1: Compared with the waitlist control, a therapist-facilitated VR intervention will reduce social anxiety symptoms at the 1-month (posttreatment) follow-up.H2: Compared with the waitlist control, a therapist-facilitated VR intervention will reduce social anxiety symptoms at the 3-month follow-up.H3: The VR intervention will demonstrate a cost per unit reduction in social anxiety symptoms, providing an estimate of its economic feasibility.

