### Recruitment

The trial will enroll 90 participants, allocating 45 to each arm. Allowing for 15% attrition, this sample provides 90% power to detect a treatment effect at T1, assuming an independent samples 2-tailed *t* test, an *α* level of .05, and Cohen *d* of 0.75. The target size also accords with comparable 2-arm VR intervention studies [16].

The first participant was enrolled in March 2026. The study will recruit participants from various settings in Hong Kong, including middle schools, tertiary institutions, and community centers. Adequate participant enrollment will be facilitated through partnerships with collaborating institutions, which will post digital flyers and promotional videos on their social-media platforms to reach the target population. The participants’ inclusion criteria were as follows: youth aged 15 to 25 years with a score of 25 or higher on the Social Phobia Inventory (SPIN). The exclusion criteria were as follows: (1) inability to attempt a baseline assessment (eg, due to being unpermitted to leave a psychiatric ward); (2) photosensitive epilepsy or significant visual, auditory, or balance impairment; (3) currently receiving another intensive psychological intervention; (4) a history of neurological conditions (eg, traumatic brain injury); and (5) insufficient language proficiency to understand the intervention requirements. In this trial, any endorsement of suicidal ideation will trigger crisis intervention procedures. Participants will be promptly flagged, and a trained clinician will notify the school or guardian to ensure appropriate safety measures are taken. School tutors or social workers familiar with students’ mental health will help identify participants unsuitable for the study, especially those whose conditions may be masked in self-report questionnaires. Participants will be recruited and screened online or offline, but will complete all interventions offline. Participants will be briefed through tutorial video clips demonstrating the research flow regarding intervention procedures, timing, and frequency.

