#### Cost Analysis

The cost analysis will encompass the following components: (1) personnel costs, including expenses for the training and recruitment of mental health professionals; (2) VR equipment and software costs, such as VR headsets and software licenses; and (3) materials and supplies (eg, office supplies, printing, and miscellaneous). The total cost will be divided by the average reduction in SPIN scores to calculate the cost per unit reduction in SPIN score.

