### Implications and Future Directions

If the intervention shows preliminary efficacy and acceptability, the findings may inform the design of a larger trial with longer follow-up and a more rigorous comparator condition. Future studies should consider active control groups, such as therapist-led psychoeducation, nonimmersive digital interventions, standard CBT-informed support, or another credible psychological control condition. Such designs would help distinguish the specific contribution of VR from nonspecific effects, such as therapist attention, expectancy, and structured contact. The exploratory cost analysis may also provide initial information on the resources required to deliver the intervention, including therapist time, training, supervision, equipment, software, and administrative costs. However, this trial will estimate the cost per unit reduction in SPIN scores rather than establish full cost-effectiveness in routine clinical or community settings.

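### H3 is listed as a hypothesis, but any positive SPIN reduction would satisfy it; it should be an exploratory estimate, as the rest of the article treats it

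*Protocol article*

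**What the plan says.** Research Objectives and Hypotheses lists three hypotheses. H1 and H2 each name the waitlist comparator and a time point (1 month and 3 months). H3 names neither: "The VR intervention will demonstrate a cost per unit reduction in social anxiety symptoms, providing an estimate of its economic feasibility". The matching research question reads "What is the cost per unit reduction in the SPIN score (if applicable" (the bracket closes the question), and the condition is not defined.

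Cost Analysis gives the computation: "The total cost will be divided by the average reduction in SPIN scores to calculate the cost per unit reduction in SPIN score". It does not say whether the reduction is the difference between arms or the change within the VR arm, or whether it is taken at T1 or T2.

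Other sections give the result a different status. The abstract says "An exploratory cost analysis will estimate the cost per unit reduction in SPIN scores". Expected Findings states hypotheses only for SPIN and places cost per unit reduction among the exploratory findings, as does the closing Conclusions section. Implications and Future Directions says "this trial will estimate the cost per unit reduction in SPIN scores rather than establish full cost-effectiveness in routine clinical or community settings".

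**The concern.** A hypothesis should be a statement that the data could contradict. Cost is always positive, so the ratio in Cost Analysis is a positive number whenever the average reduction is above zero, however small. As worded, only the sign of a point estimate can contradict H3.

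A trial in which H1 and H2 both fail could therefore still describe H3 as supported and offer the ratio as evidence of economic feasibility. A bare ratio would also hide that its denominator may be compatible with zero, in which case cost per point has no finite upper limit. The article motivates the economic work by policymakers' resource allocation, so a single unqualified figure could be taken further than the data allow.

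**Working it through.** **Inputs from the article.** From Recruitment: 45 per arm (90 in total), a two-sided t test at the 5% level, d = 0.75, and entry at SPIN 25 or higher. The power statement there is "Allowing for 15% attrition, this sample provides 90% power to detect a treatment effect at T1". From Primary Outcomes: SPIN, a test-retest r of 0.73.

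**Assumed, because the article does not give them.** Source-population SPIN mean of 15 to 30 and SD of 10 to 13, normally distributed.

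**1. The plan's own figure.** n per arm = 2(1.960 + 1.282)² / 0.75² = 37.4, rounded up to 38. Allowing for 15% attrition, 38 / 0.85 = 44.7, rounded up to 45, so 90 in total. The stated size is reproduced. (The exact t calculation gives 39 per arm, then 46 after attrition, 92 in total, which is close.) The steps below use 38 completers per arm.

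**2. No treatment effect, between-arm reading.** The estimated difference is symmetric about zero, so P(difference > 0) = 50%. This needs no outside assumption.

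**3. No treatment effect, within-arm reading.** For population mean μ and SD σ, let a = (25 − μ)/σ and λ = φ(a)/[1 − Φ(a)].
- Expected drop from regression to the mean = (1 − r)σλ.
- Baseline variance after selection: v = σ²(1 + aλ − λ²).
- Variance of change = v(1 − r)² + σ²(1 − r²).
- P(mean reduction > 0) = Φ(drop / √(variance of change / 38)).

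| μ / σ | Expected drop (points) | SE of mean change | P(reduction > 0) |
|---|---|---|---|
| 15 / 10 | 4.12 | 1.13 | over 99.9% |
| 20 / 12 | 3.50 | 1.36 | 99.5% |
| 25 / 13 | 2.80 | 1.48 | 97.1% |
| 30 / 13 | 2.00 | 1.49 | 91.0% |
| 30 / 10 | 1.37 | 1.15 | 88.4% |

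The last row is the lowest value over the assumed range.

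**4. Precision of the ratio at the planned effect.** Treat cost as fixed.
- Unadjusted: 0.75 ± 1.99 × √(2/38) = 0.75 ± 0.457, or 0.29 to 1.21 SD. Cost per point spans a factor of 1.207 / 0.293 = 4.1.
- Baseline-adjusted: the standard error is multiplied by √(1 − ρ²), where ρ is the baseline to follow-up correlation among those enrolled. Entry at 25 or higher narrows the baseline SD to s = √v, so ρ = rs / √(r²s² + σ²(1 − r²)). At 15/10, s = 4.46 and ρ = 0.43; at 30/10, s = 6.97 and ρ = 0.60. The intervals are 0.337 to 1.163 and 0.383 to 1.117, giving factors of 3.45 and 2.9. Using r = 0.73 unchanged would ignore the truncation and overstate the precision.

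**5. A small observed effect.** At an observed 0.2 SD, the interval is 0.2 ± 0.457 = −0.26 to 0.66 SD. It includes zero, so cost per SD has no finite upper limit, yet H3 as worded would be met.

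**The case against.** The strongest reply is that no test of H3 is planned. The sentence itself ends in the language of estimation, the significance level appears under Primary Analysis for SPIN, and several sections label the cost work exploratory or disclaim cost-effectiveness. This largely stands. A reader might infer that the trial carries a false-positive rate of 50% to nearly 100% for H3. The article does not support that, because it states no confirmation rule. The percentages show only how easily the wording is satisfied. But if H3 means no more than that a ratio will be estimated, it is an objective placed in a list of hypotheses, and the remedy is the same.

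A reader might also infer that 'if applicable' means an unfavourable ratio would be dropped. The phrase sits in the research question, not in H3, and is undefined. It could equally mean that the ratio is given only if a reduction on SPIN is established. If that meant a significant benefit over waitlist, the no-effect rate would be about 2.5% per time point. The text does not settle it.

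Two further limits stand. The figures near 90% and above need the within-arm reading and the assumed means and SDs. And an interval method for a cost ratio may properly be left to an analysis plan, so its absence is not the defect here.

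**Conclusion.** The point holds as one of wording and status. H3 is presented as something the intervention will demonstrate, with no criterion that an ineffective programme would fail except by the sign of an estimate. This conflicts with the exploratory status given to the same quantity elsewhere.

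The 50% figure rests only on the between-arm reading. The range from 88% to nearly 100% is conditional on the within-arm reading and the population assumptions. At the planned effect with 38 completers per arm, the ratio is uncertain about 4-fold unadjusted, or about 3- to 3.5-fold after baseline adjustment that allows for truncated entry.

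The consequence is confined to how the economic result may be reported. It is worth correcting before analysis, but it does not threaten the trial's main conclusions.

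**What to change.** - Remove H3 from the hypotheses and restate it as an exploratory estimation objective, in line with the abstract, Expected Findings and Conclusions.
- Replace 'if applicable' with a commitment always to report the incremental cost of VR over waitlist and the between-arm SPIN difference at one named time point, each with a 95% interval, whatever the direction.
- Give the cost per point with a Fieller or bootstrap 95% interval.
- Where the interval for the SPIN difference includes zero, state that the ratio has no finite upper limit and that no conclusion on economic feasibility is drawn.

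The ratio should not be reported only when SPIN is significant. That would be another form of conditional reporting and would favour overestimated effects, so understating cost per point.

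The cost is a few sentences and a short calculation on data already planned. The downside is that H3 can no longer be reported as confirmed, and the ratio will carry a wide interval.

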## Methods

### Trial Design

The design is a 2-arm, statistician-blind, parallel-group RCT to test whether the VR intervention, compared with a waitlist control condition, leads to a reduction in social anxiety among youth. Assessments will be carried out at 0 (baseline, T0), 1 (posttreatment, T1), and 3 (follow-up, T2) months. A summary of the trial design can be seen in Figure 1.

**Figure 1. F1:**
[figure not shown]
CONSORT (Consolidated Standards of Reporting Trials) flow diagram of the proposed randomized controlled trial. VR: virtual reality.

### Ethical Considerations

The protocol and the informed consent form received approval from the Hong Kong Shue Yan University Human Research Ethics Committee (HREC 24-05(M3)). Eligible participants willing to join the study will sign an online consent form. For participants under 18 years of age, additional parental or guardian consent will be obtained. To reduce the likelihood or detection of harm, various safety and security procedures will be implemented, such as excluding potentially psychologically ill participants during the screening stage.

To ensure the confidentiality and security of participant data, all collected information is securely encrypted during transmission and storage, preventing unauthorized access. Access to participant data is strictly limited to authorized research personnel. Additionally, personally identifiable information is anonymized or deidentified wherever possible to safeguard participant privacy. Each eligible participant will receive compensation of approximately HK $500 (HK $1=US $0.128 as of July 15, 2026) for their participation in the study.

### Randomization, Allocation Concealment, and Blinding

Participants will be randomized after the baseline assessment using computer-generated block randomization with a 1:1 allocation ratio within pre-established blocks of 90 participants. To ensure balance, a randomized blocking schema with block sizes of 2, 4, or 6 will be implemented. An independent research assistant, uninvolved in statistical analysis, will conduct the randomization. Allocation concealment will be maintained until the participant has completed eligibility screening, provided informed consent, and undergone baseline assessment. The allocation sequence will be accessible only to the independent staff member responsible for randomization. Research staff involved in recruitment and baseline assessment will not have access to the allocation sequence before assignment. Because of the nature of the VR intervention and the waitlist control condition, participants and therapists cannot be blinded after allocation. However, the statistician conducting the primary analysis will remain blinded to group labels until the primary analysis has been completed. Group labels will be coded as group A and group B during data cleaning and primary analysis to reduce analytic bias.

### Recruitment

The trial will enroll 90 participants, allocating 45 to each arm. Allowing for 15% attrition, this sample provides 90% power to detect a treatment effect at T1, assuming an independent samples 2-tailed *t* test, an *α* level of .05, and Cohen *d* of 0.75. The target size also accords with comparable 2-arm VR intervention studies [16].

The first participant was enrolled in March 2026. The study will recruit participants from various settings in Hong Kong, including middle schools, tertiary institutions, and community centers. Adequate participant enrollment will be facilitated through partnerships with collaborating institutions, which will post digital flyers and promotional videos on their social-media platforms to reach the target population. The participants’ inclusion criteria were as follows: youth aged 15 to 25 years with a score of 25 or higher on the Social Phobia Inventory (SPIN). The exclusion criteria were as follows: (1) inability to attempt a baseline assessment (eg, due to being unpermitted to leave a psychiatric ward); (2) photosensitive epilepsy or significant visual, auditory, or balance impairment; (3) currently receiving another intensive psychological intervention; (4) a history of neurological conditions (eg, traumatic brain injury); and (5) insufficient language proficiency to understand the intervention requirements. In this trial, any endorsement of suicidal ideation will trigger crisis intervention procedures. Participants will be promptly flagged, and a trained clinician will notify the school or guardian to ensure appropriate safety measures are taken. School tutors or social workers familiar with students’ mental health will help identify participants unsuitable for the study, especially those whose conditions may be masked in self-report questionnaires. Participants will be recruited and screened online or offline, but will complete all interventions offline. Participants will be briefed through tutorial video clips demonstrating the research flow regarding intervention procedures, timing, and frequency.

